Studies showed that CHM could be an alternative monotherapy or adjunctive therapy for adults with IMN. Two case reports suggested that 1 year treatment of the herb *Astragalus membranaceus* Fisch. ex Bunge alone was associated with complete remission in patients who were presenting with nephrotic syndrome and resistant to cyclosporine and mycophenolate (Ahmed et al., 2007; Leehey et al., 2010). A retrospective case series comprised of 15 IMN cases who did not respond to immunosuppressive therapies received 6 months treatment of Jian Pi Qu Shi formula, and 80% of them reached complete or partial remission on the 12th month after treatment (Shi et al., 2018). Chen et al. reported a randomized controlled trial that compared multi-ingredient CHM to conventional immunosuppression with prednisone and cyclophosphamide for IMN patients with nephrotic proteinuria (urinary protein excretion ≥3.5g/24h) (Chen et al., 2013). Composite remission (either complete or partial remission) showed a similar rate in the two arms at 48 weeks (73% vs. 78%) (Chen et al., 2013). Liu et al. compared the remission between IMN patients who received tripterygium glycosides tablets (compound of the herb *Tripterygium wilfordii* Hook.f.) plus prednisone and who received tacrolimus plus prednisone (Liu et al., 2015). Both composite remission (86.9% vs. 90.0%) and complete remission (52.2% vs. 46.7%) were similar between the two groups at 36 weeks (Liu et al., 2015).

These findings were obtained in the setting of clinical trials and need validation in daily clinical practice, as the treatment scenario of CHM is more complicated in practice than that in trials. Instead of a fixed formula or proprietary CHM used through the whole research period in clinical trials, prescriptions of CHM are individualized and changed flexibly based on syndrome differentiation or state of the illness in clinical practice. Therefore, we proposed the first registry-based cohort study of INM in China.

The aims of this registry-based cohort include (but are not limited to):

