### Interventions

This observational study is designed to evaluate the effectiveness of CHM in a real-word hospital setting. Therefore, there are neither treatment protocols nor interference with therapeutic schedules for the included participants. But the information of therapeutic regimens will be collected to identify the exposure of CHM. Exposure of CHM includes either oral or intravenous administration proprietary CHM products and oral administration CHM formulas. Low, moderate, and high level of CHM exposure will be defined as the cumulative exposure time of CHM accounts for 25, 50, and 75% of individual follow-up time. The individual follow-up time will be from the baseline visit to the last visit or the end of the study.

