### Enrollment and Follow-Up

This study is designed to be a long-term longitudinally extensible cohort. The study aims to include 2000 Chinese IMN adults. The recruitment is estimated to take 42 months, from July 2020 until December 2023. The patients who meet the inclusion criteria will be enrolled continuously. Both incident patients and prevalent patients will be recruited by physicians in nephrology clinics and inpatient departments in 11 participating sites. Incident patients are individuals who are newly diagnosed and first initiated on treatments. Prevalent patients are individuals who have already been diagnosed as IMN and have been receiving treatments before the study. Meanwhile, the electronic medical record in 11 participating sites will be retrospectively screened to recruit the confirmed cases.

Individuals who are eligible and consent to participate will be invited to attend a baseline visit. Participants will be followed for up to at least 2 years. Participants who experience the primary endpoint (remission) will be continued to be followed up until the end of the study or death. The schedule of follow-up visits is presented in Figure 1. Follow-up visits will occur quarterly in the first year after enrollment and then semi-annually from the second year. The baseline, semi-annual, and annual follow-up visits in the first year and annual visits from the second year are required in-person visits. All other visits can be in-person or remote via telephone call or smartphone applications. In order to retain participants and minimize the number of dropouts and withdraws as well as the missing data, a reasonably flexible visit time window within a range of 4 weeks forward or backward from the scheduled visit day will be acceptable.

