### Statistical Plan

Attempting to ensure equivalence in baseline characteristics of participants between the CHM group and the conventional therapy group, a propensity score method will be performed. Variables involving age, sex, proteinuria, eGFR, serum albumin, uric acid, PLA2R antibody level, and pathological type will be included into the logistic regression model to calculate a propensity score for each participant. Participants who are exposed to CHM will be matched to those who receive conventional drugs alone based on the propensity score, using the greedy matching with a standard calliper width of 0.2 and without case replacement. Covariate balance of the matched cohort will be assessed using the mean standardized differences. When a |d| > 0.10, it is considered as an imbalance. Inverse probability of treatment weighting based on the propensity score will also be performed to evaluate the robustness of the matching results.

Baseline demographic variables will be presented as means, medians, or percentages, and using Chi-square test, independent t test, or Mann-Whitney *U* test, as appropriate. Outcomes of composite remission, CR, PR, no response, death, relapse, and composite endpoint will be analysed by using Chi-square test and logistic regression. Odd ratios and 95% confidence intervals will be estimated. Time to remission will be analysed by using Cox regression model, adjusting for gender, age, baseline proteinuria, GFR, PLA2R antibody level, uric acid, Chinese medicine syndrome, and propensity score.

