## Discussion

This national-wide, prospective, observational registry provides a platform for multi-center longitudinal research in IMN. During the first 5-year research phase of the registry, it is expected to provide a description of treatment patterns in patients with IMN in China, and more than that, to provide an estimation of the clinical remission of this population undergoing various therapeutic regimens in daily practice.

Quality control is vital in clinical studies, especially in multicenter studies. Our multicenter registry uses EDC to collect data and promote the quality of the data. Instead of finding errors after the data collection period, EDC allows researchers to build logical checks and pre-fillable answers, which can reduce the number of errors in the data at the collection site. Further, EDC keeps all traces of operation to ensure the authenticity of data.

Several bias may occur in a cohort. The nature of the cohort study could induce the participant selection bias, such as referral bias. As all 11 centers that participated in the study are tertiary-care hospitals, patients recruited from the centers with a particular severity differ from those in the community or general population, especially among prevalent patients (i.e., individuals who have already been receiving treatments before enrollment). Considering the incidence of IMN and the availability of subjects, in order to recruit enough samples on time, our cohort will include both incident patients who are newly diagnosed and first initiated on treatments and prevalent patients. Subgroup analysis of incident patients and prevalent patients will be performed to investigate whether the results are robust among the whole sample and different risk of subgroups and overcome the referral bias. In addition, in order to minimize the risk of selection bias, a propensity score approach will be used to balance the baseline characteristics of the CHM group and conventional group.

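### The split between CHM-exposed patients and the conventional-drugs-only comparator has no time window or prior-CHM rule, so former CHM users among prevalent patients can enter the comparator unadjusted

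*Protocol article*

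**What the plan says.** All references are to the protocol article.

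- **Interventions, what counts as CHM.** Exposure is defined by product and route: "Exposure of CHM includes either oral or intravenous administration proprietary CHM products and oral administration CHM formulas". No period, minimum duration or look-back is given.
- **Interventions, exposure levels.** Low, moderate and high exposure are set where the "cumulative exposure time of CHM accounts for 25, 50, and 75% of individual follow-up time". The denominator is then fixed: "The individual follow-up time will be from the baseline visit to the last visit or the end of the study". Under Statistical Plan these levels appear only as a subgroup factor.
- **Statistical Plan, main comparison.** "Participants who are exposed to CHM will be matched to those who receive conventional drugs alone based on the propensity score". No window is attached to either side of this split.
- **Enrollment and Follow-Up.** Incident and prevalent patients are both recruited. "Prevalent patients are individuals who have already been diagnosed as IMN and have been receiving treatments before the study". Neither this section nor Eligibility Criteria states a washout or a rule on earlier CHM.
- **Statistical Plan, adjustment.** "Variables involving age, sex, proteinuria, eGFR, serum albumin, uric acid, PLA2R antibody level, and pathological type will be included" in the propensity model. The Cox model for time to remission adds Chinese medicine syndrome and the propensity score to a similar list. Prior CHM, other prior treatment and incident/prevalent status are in neither.
- **Outcomes, Table 1.** Partial remission needs a fall of at least 50% from peak proteinuria to a level between 0.3 and 3.5 g/24 h. No response, by contrast, is judged from baseline.
- **Discussion.** "Subgroup analysis of incident patients and prevalent patients will be performed".

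**The concern.** The main contrast is meant to show how patients on CHM fare against patients treated without it. For an incident patient, treatment history starts at about enrolment, so the labels are clear. A prevalent patient may have had a long CHM course that ended before the baseline visit. If that patient now takes conventional drugs, nothing in the text keeps them out of the comparator, and nothing in the models accounts for the earlier course.

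This is unlikely to be a rare case. Study Setting names 11 sites, and all but the two people's hospitals (Zhaoqing and Yue Bei) are Chinese or integrative medicine institutions.

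The partial remission definition adds to the problem. A peak that predates enrolment lets a response obtained on CHM be credited to the treatment in use after enrolment. The pooled matched estimate, which is the main effectiveness result, would then compare CHM with a mixture of never users and former users in unknown proportion.

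**Working it through.** **1. Does the stated clock settle the binary split?** No. It is the denominator of the graded levels. The binary split rests on product and route on one side and on receipt of conventional drugs only on the other, without dates. That a former user lands in the comparator is the natural reading of the present tense and of a clock that ignores pre-enrolment use. It remains an inference.

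**2. Does anything else exclude or adjust for former users?** Eligibility has no prior-CHM criterion. The propensity variables are age, sex, proteinuria, eGFR, albumin, uric acid, PLA2R antibody and pathological type. The Cox covariates are gender, age, baseline proteinuria, GFR, PLA2R antibody, uric acid, Chinese medicine syndrome and the propensity score. None records past treatment.

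**3. How can an earlier response count after enrolment?** Let P be peak and B baseline proteinuria. The proteinuria part of partial remission is already met at enrolment if B lies between 0.3 and 3.5 g/24 h and B ≤ P/2. With P = 7.0 (2 × 3.5), any B in that range qualifies. A patient matched on the same B whose peak equals B must still halve it. Matching on baseline proteinuria does not remove this difference, because peak is not in the model.

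**4. Can the bias be sized?** The article gives no figure for prior CHM, so there is none to reproduce. Sample Size gives 73.7% remission under immunosuppressive agents and 67.0% under CHM alone or combined (75/112 = 66.96%, which agrees). Let f be the share of former users in the comparator and r their remission rate. Both are assumptions.

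- Comparator rate = (1 − f) × 73.7 + f × r
- Difference from the CHM group = comparator rate − 67.0
- Shift in the difference = f × (r − 73.7)

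| f (assumed) | Difference if r = 67.0 | Difference if r = 73.7 | Limits, r from 0 to 100 |
|---|---|---|---|
| 10% | 6.03 points | 6.70 | −0.67 to 9.33 |
| 30% | 4.69 points | 6.70 | −15.41 to 14.59 |
| 50% | 3.35 points | 6.70 | −30.15 to 19.85 |

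The sign of the shift depends only on whether r is below or above 73.7. With r = 67.0 the difference is (1 − f) × 6.7, so the relative attenuation equals whatever f was assumed. That column contains no information from the documents about the actual bias.

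**The case against.** **The cited clock governs something else.** This stands. A reader might infer that the baseline-start sentence itself makes former users unexposed. It does not: it sets the denominator for a subgroup factor. The fault lies in the undated binary split, and the clock shows only that no other rule captures pre-enrolment use.

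**Counting exposure from enrolment is coherent.** This also stands. The primary outcome is at 24 months after enrolment and time to remission runs from enrolment. If the target is treatment during follow-up, a former user now on conventional drugs is labelled correctly and past CHM is a confounder. A reader might infer that adjustment could not help. Under that target it could, but the listed models do not include it.

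**Bias toward the null is not shown.** A reader might infer attenuation, for example by 30%. The documents do not support this. The peak-proteinuria route would raise remission in the comparator and widen the 73.7 v 67.0 gap. Former users could also be patients in whom CHM failed. The 67.0% describes patients who received CHM alone or in combination, not patients who had stopped it.

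**The background does not prove carry-over.** The Introduction describes a 15-case series whose patients "received 6 months treatment of Jian Pi Qu Shi formula, and 80% of them reached complete or partial remission on the 12th month after treatment". It does not say whether the 12 months run from the start or the end of the course, so it is at most suggestive.

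**The incident/prevalent subgroup deals with it.** Only in part. Incident patients are newly diagnosed and starting treatment, so their estimate is largely free of the problem, and a discrepancy between subgroups would be a warning. The subgroup does not correct the pooled match or the prevalent estimate.

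**Look-back detail belongs in the full protocol.** An article may leave out such detail. But this one does state the comparator, the exposure clock and the covariate lists, and run as written they leave pre-enrolment CHM unhandled.

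**Conclusion.** The point holds as a gap in how the main comparison is defined. The binary split has no time window or prior-CHM rule, prevalent patients are pooled into the match, and neither covariate list includes prior CHM or incident/prevalent status. Former CHM users now on conventional drugs can therefore enter the comparator unadjusted.

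The direction and size of the bias cannot be determined from the documents. The table under working shows only how far the answer depends on two unknowns. That former users are common at these sites is plausible from the 9 of 11 site count, but their share is not reported. The conclusion assumes that the full protocol has no look-back rule beyond what the article shows. The change should be made, because it affects the main effectiveness estimate and costs little.

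**What to change.** 1. State the time window for the binary split, and classify every participant at baseline as a never, former or current CHM user since diagnosis, from medical history and hospital records.
2. In the main match, limit the conventional-drugs-only comparator to patients with no CHM since diagnosis. Report former users now on conventional drugs as a separate group.
3. Add prior CHM use and incident/prevalent status to the propensity model for the pooled analysis that keeps former users. In the restricted match the comparator has no prior CHM by construction, so only incident/prevalent status can be balanced there.
4. Keep the exposure share as defined on post-baseline time. Do not add pre-enrolment months to it: a share of follow-up time could then exceed 100%, and exposure from before and after the start of the outcome clock would be mixed.

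**Cost.** Medical history and prescriptions are already collected and records are screened for recruitment, so at most a history field and a definition are needed. The visit schedule figure is not shown, so the field may already exist. The planned before/after prescription comparison addresses performance bias and should not be relied on for patient-level history.

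The main downside is a smaller comparator. Take 2000 enrolled, 10% lost and an assumed 1:1 split: 2000 × 0.9 / 2 = 900 controls. If 10%, 30% or 50% were former users, 810, 630 or 450 would remain. Older prescriptions will also carry some record or recall error.

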### Enrollment and Follow-Up

This study is designed to be a long-term longitudinally extensible cohort. The study aims to include 2000 Chinese IMN adults. The recruitment is estimated to take 42 months, from July 2020 until December 2023. The patients who meet the inclusion criteria will be enrolled continuously. Both incident patients and prevalent patients will be recruited by physicians in nephrology clinics and inpatient departments in 11 participating sites. Incident patients are individuals who are newly diagnosed and first initiated on treatments. Prevalent patients are individuals who have already been diagnosed as IMN and have been receiving treatments before the study. Meanwhile, the electronic medical record in 11 participating sites will be retrospectively screened to recruit the confirmed cases.

Individuals who are eligible and consent to participate will be invited to attend a baseline visit. Participants will be followed for up to at least 2 years. Participants who experience the primary endpoint (remission) will be continued to be followed up until the end of the study or death. The schedule of follow-up visits is presented in Figure 1. Follow-up visits will occur quarterly in the first year after enrollment and then semi-annually from the second year. The baseline, semi-annual, and annual follow-up visits in the first year and annual visits from the second year are required in-person visits. All other visits can be in-person or remote via telephone call or smartphone applications. In order to retain participants and minimize the number of dropouts and withdraws as well as the missing data, a reasonably flexible visit time window within a range of 4 weeks forward or backward from the scheduled visit day will be acceptable.

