## Abstract

**Introduction:** Some encouraging findings of Chinese herbal medicine (CHM) in management of idiopathic membranous nephropathy (IMN) obtained in the setting of clinical trials are hard to validate in the daily clinical practice due to a complicated treatment scenario of CHM in practice. The primary objective of this registry is to provide a description of treatment patterns used in management of IMN and assess clinical remission in daily practice in a Chinese population sample with IMN.

**Methods and analysis:** This is a prospective, multicenter cohort which will comprise 2000 adults with IMN regardless of urinary protein levels that will be recruited from 11 nephrology centers across China. The participants will be followed for up to at least 2 years. Primary outcome is composite remission (either complete remission or partial remission) 24 months after enrolment. The secondary outcomes are complete remission, partial remission, time to remission, no response, relapse, proteinuria, annual change of glomerular filtration rate, antibodies against PLA2R, and composite endpoint of 40% reduction of glomerular filtration rate, doubling of serum creatinine, end-stage renal disease, and death. Propensity score analysis will be used for matching and adjustment.

**Ethics and dissemination:** This study has been approved by the Ethics Committee of Guangdong Provincial Hospital of Chinese Medicine (BF2020-094-01). Results of the study will be published in both national and international peer-reviewed journals, and presented at scientific conferences. Investigators will inform the participants as well as other IMN patients of the findings via health education.

**Study registration**: ChiCTR2000033680 (prospectively registered).

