### Eligibility Criteria

Eligible candidates for the study are IMN patients of any risk levels to capture a broad spectrum of clinical presentations. Inclusion criteria include Chinese adults aged from 18 to 85 years old; diagnosis of biopsy-proven IMN or antibodies against phospholipase A2 receptor (PLA2R)-positive patients who are not associated with other diseases which cause secondary MN, such as systemic lupus erythematous, infections with hepatitis B virus, hepatitis C virus, or syphilis, sarcoidosis, and cancer. Patients with the following criteria will be excluded: patients with a GFR less than 15 ml/min/1.73 m^2^; patients with comorbidities including malignant cancers, decompensated cirrhosis, hematologic diseases, and mental diseases.

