### Outcomes

The primary outcome is clinical composite remission at 24 months after enrollment. Composite remission is defined as either complete remission (CR) or partial remission (PR). Secondary outcomes are CR, PR, time to remission (CR, PR, and CR or PR), no response, relapse, urine protein excretion, urinary protein creatinine ratio, serum albumin, annual change of GFR (GFR slope), PLA2R, adverse events, and composite endpoint of 40% reduction of GFR, doubling of serum creatinine, end-stage renal disease (ESRD), and death. The outcome variables and definitions are presented in Table 1.

**TABLE 1 T1:** Outcome variables and definitions.

Outcome variables	Definitions
Primary outcome	
Composite remission	Either complete remission or partial remission
Secondary outcomes	
Complete remission (CR)	A reduction of proteinuria to ≤0.3g/24 h accompanied by a normal serum albumin and a normal Scr. Beck et al. (2013)
Partial remission (PR)	At least 50% reduction from peak value of proteinuria to a level between 0.3 and 3.5 g/24 h, accompanied by an improvement or normalization of serum albumin and a stable Scr. Beck et al. (2013)
Relapse	The development of proteinuria ≥3.5 g/24 h after a CR or PR
Time to complete remission	Days from enrollment to CR
Time to partial remission	Days from enrollment to PR
No response	No reduction in proteinuria of at least 25% from baseline
Serum albumin	/
Urine protein excretion	Urine protein excretion within 24 h
Urinary protein-to-creatinine ratio (UPCR)	/
Antibodies against PLA2R	/
Doubling of serum creatinine	Doubling increase of serum creatinine from baseline
40% reduction of eGFR	A reduction in eGFR of 40% from baseline. Serum creatinine based eGFR is calculated using the Chronic Kidney disease Epidemiology Collaboration (CKD-EPI) equation
End-stage renal disease (ESRD)	eGFR ≤15 ml/min/1.73m^2^ or commencement of renal replacement treatment
Composite endpoint	ESRD or 40% reduction of eGFR or doubling of serum creatinine
eGFR slope	Annual change in eGFR

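### Prevalent patients already in complete or partial remission at enrolment are not separated out of the remission analyses, so maintained remission can be counted as 24-month success

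*Protocol article*

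**What the plan says.** **Who enters.** The Abstract describes "2000 adults with IMN regardless of urinary protein levels". Eligibility Criteria adds: "Eligible candidates for the study are IMN patients of any risk levels to capture a broad spectrum of clinical presentations". The exclusions are "patients with a GFR less than 15 ml/min/1.73 m^2^; patients with comorbidities including malignant cancers, decompensated cirrhosis, hematologic diseases, and mental diseases"; current remission is not among them. Enrollment and Follow-Up admits incident and prevalent patients, and says of the latter: "Prevalent patients are individuals who have already been diagnosed as IMN and have been receiving treatments before the study".

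**What is counted.** Under Outcomes, "The primary outcome is clinical composite remission at 24 months after enrollment". Composite remission is CR or PR. In Table 1, CR is "A reduction of proteinuria to ≤0.3g/24 h accompanied by a normal serum albumin and a normal Scr". PR is "At least 50% reduction from peak value of proteinuria to a level between 0.3 and 3.5 g/24 h", with better or normal albumin and stable creatinine. Time to CR is "Days from enrollment to CR", and time to PR has the same origin. No response means that proteinuria has not fallen by at least 25% from baseline.

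**How it is analysed.** The Statistical Plan matches patients exposed to Chinese herbal medicine (CHM) to patients on conventional drugs alone. The propensity score uses age, sex, proteinuria, eGFR, albumin, uric acid, PLA2R antibody and pathological type. Inverse probability weighting is the robustness check. Remission outcomes go to chi-square tests and logistic regression, and time to remission to a Cox model that also adjusts for baseline proteinuria. Incident versus prevalent is one of a long list of subgroups; the Discussion offers it as an answer to referral bias.

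**The concern.** Two reference points are in use. PR looks back to the peak, which for a treated prevalent patient can lie before enrolment. Time to remission and no response look back to enrolment. Nothing stated requires a patient to be out of remission on day 0.

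The primary outcome therefore mixes two quantities: remission newly achieved during follow-up, and remission that was present at entry and has lasted. The second group says nothing about which regimen induces remission.

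- If the share in remission at entry is similar in the CHM and conventional groups, the contrast is diluted.
- If the share differs, part of the contrast reflects treatment given before the study. CHM exposure is counted from the baseline visit (Interventions), so a remission achieved earlier on another regimen can be credited to CHM.

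The time-to-remission analysis has a separate problem: a patient already in remission at the time origin is not at risk of the event being modelled.

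**Working it through.** **1. One patient against the Table 1 definitions.** Take a prevalent patient with a pre-study peak of 8 g/24 h who enrols at 2 g and is still at 2 g at month 24, with improved albumin and stable creatinine. Read the peak as including pre-study values.

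- PR: fall from peak = (8 − 2)/8 = 75%, at least 50%, and 2 g lies between 0.3 and 3.5 g. PR is met on day 0 and at month 24.
- Composite remission at 24 months: success.
- No response: fall from baseline = (2 − 2)/2 = 0%, below 25%. This is also met.
- Time to PR: zero days, or an event before the origin.

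A patient in stable CR at entry likewise meets CR and no response together. This conflict follows from the definitions at any prevalence.

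**2. The plan's own figure.** Sample Size gives 73.7% (immunosuppressive agents), 67.0% (CHM alone or combined, 75/112), 10% loss, two-sided alpha 0.05, 2000 patients and 80% power. For two proportions at 1:1:

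n = [1.96·√(2·0.7035·0.2965) + 0.8416·√(0.737·0.263 + 0.670·0.330)]² / 0.067² = 729 per group.

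That is 1458 in total, and 1458/0.9 = 1620 enrolled. With 1800 evaluable at 1:1, power is 87.6%. The stated 2000 at 80% is not reproduced at 1:1; it is reached with a split of about 2.5:1, which the article does not state. The present point does not depend on this, and 1:1 is used below only for illustration.

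**3. Dilution.** Let f be the share in remission at entry, equal in both groups, and m the proportion of them still in remission at month 24, also equal. Each group's rate is f·m + (1 − f)·p, so m cancels and the difference is (1 − f)·0.067.

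The documents do not give f. Assume 30-50% of patients are prevalent and 30-50% of those are in remission: f = 0.30·0.30 = 9% to 0.50·0.50 = 25%, or 180 to 500 of 2000.

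- f = 9%: 0.91·6.7 = 6.1 points
- f = 25%: 0.75·6.7 = 5.0 points

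Power with 900 evaluable per group and m = 0.85:

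| f | Difference (points) | Power |
|---|---|---|
| 0 | 6.7 | 87.6% |
| 10% | 6.0 | 81% |
| 20% | 5.4 | 73% |
| 30% | 4.7 | 63% |

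With m from 0.70 to 0.90, power is 80-82% at f = 10%, 70-74% at 20% and 59-65% at 30%.

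**4. Imbalance, before any adjustment.** With no treatment effect, 25% versus 15% in remission at entry, 85% of those staying in remission and 60% new remission in the rest, the spurious difference is (0.25 − 0.15)·(0.85 − 0.60) = 2.5 points. All four inputs are assumptions.

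**The case against.** **The planned comparison is adjusted.** Matching and weighting use baseline proteinuria, albumin and eGFR, with an absolute standardised difference above 0.10 treated as imbalance. These are close to the components of CR, so baseline CR is largely captured. This stands, and it makes the 2.5 points a crude figure that should not be read as the bias of the planned analysis. It is not a full answer. Peak proteinuria, which decides PR, is not in the score, nor are prior treatment, disease duration and incident/prevalent status. Matching two patients who are both in remission also leaves the dilution in place.

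**Not every such patient is a success.** A reader might infer that anyone in remission at entry is automatically counted. The documents do not support that: the outcome is status at 24 months, so a patient who has relapsed by then is a failure.

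**Maintained remission is also an outcome of treatment.** A reader might infer that the primary outcome measures only earlier treatment. That goes too far for a registry that deliberately takes all risk levels and aims first to describe treatment patterns. The fault is that maintenance and induction are mixed in one rate.

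**The article is condensed.** Analysis sets and the handling of events before the origin may be settled in a document not shown, and the article does not say outright that all patients are pooled. It also does not say that the peak includes pre-study values. This limits certainty about the final analysis, but the definitions printed in Table 1 conflict as they stand.

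**The dilution needs a premise.** It assumes that 73.7% and 67.0% describe patients not in remission at entry. Sample Size does not say so. If those samples were already mixed, the loss is double-counted.

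**Conclusion.** The point holds in this form: patients in CR or PR at baseline can be counted as 24-month successes if they remain in remission, have no meaningful time to remission, and can satisfy PR (or CR) and no response together. The planned adjustment reduces imbalance between groups, but does not fully remove it and does not remove dilution.

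The size is unknown. Under the assumed 9-25% in remission at entry, equal shares and maintenance in both groups, and planning rates that apply only to patients not in remission, the 6.7-point contrast falls by 0.6 to 1.7 points. The residual bias after matching cannot be sized from the documents. The conflict between definitions needs none of these assumptions.

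A reader might also infer that incident patients alone should carry the main comparison. The figures do not favour that. With 30-50% prevalent, 1000-1400 incident patients enrol and 900-1260 remain after 10% loss. At 1:1 for 73.7% versus 67.0%, that gives about 60-74% power.

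**What to change.** 1. Restrict composite remission, PR, no response, time to composite remission and time to PR to patients not in CR or PR at the baseline visit.
2. Restrict CR and time to CR to patients not in CR at baseline, so that patients in baseline PR stay at risk of CR.
3. Analyse patients in remission at entry separately, for maintained remission and relapse.
4. Record pre-enrolment peak proteinuria for prevalent patients, and state in Table 1 that the peak may predate enrolment.
5. Add incident/prevalent status, disease duration and prior treatment to the propensity model.
6. Keep the incident-only estimate as a prespecified sensitivity analysis, not the lead.

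**Cost.** Recruitment and visits do not change. Baseline proteinuria, albumin and creatinine are already collected. Pre-enrolment peak is not listed under Data Collection and Management and would have to be taken from earlier records.

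The denominator shrinks: of 1800 evaluable, 1800·0.91 = 1638 to 1800·0.75 = 1350 would remain at f = 9% to 25%. On the same assumptions (1:1, full 6.7-point contrast), power is about 84% to 77%. The diluted analysis of all 1800 gives about 82% to 68% with m = 0.85, so under these assumptions the restriction costs no power.
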